## **2.7 Outcomes**

### **2.7.1 Primary Outcome**

Hip dislocation by radiographic evaluation (%).

### **2.7.2 Secondary Outcomes**

· Functional changes such as the degree of scoliosis, pain index, satisfaction with wearable medical devices for hip joint protection, hip and knee joint range of motion, discomfort in caring for patients, and changes in the overall quality of life of patients through simple radiographic examination.

#### **A. Joint range of motion**

Measure the joint range of motion of the patient's hip and knee using a goniometer.

- I. abduction with hip at 90° flexion
- II. Hip abduction with hip at 0° flexion
- III. Hip adduction with hip at 0° flexion
- IV. Hip flexion contracture (Thomas test)
- V. Popliteal angle

#### **B. Questionnaire evaluation**

I. Pain index (Visual analog scale): In the case of children with cerebral palsy GMFCS IV and V, communication is difficult, so the patient's hip pain felt by the guardian is evaluated.

#### **C. Likert scale**

Satisfaction evaluation of wearable medical device for hip joint protection

Example of this study questionnaire: Very satisfied - Satisfied - Moderate - Somewhat dissatisfied - Very dissatisfied

#### **D. Child Health Index of Life with Disabilities (CPCHILD)**

This tool consists of 9 items as a tool to evaluate the quality of life of patients with severe cerebral palsy. The guardian evaluates, and each item is scored on a scale of 0 to 5, and each item is as follows. Investigate hip contracture-related items among CPGHILDs, such as daily activities, posture/movement, comfort and emotion, the child's overall quality of life, and the importance of items related to the child's quality of life

## **2.8 Study Design**

### **2.8.1 Overall Design**

Multicenter, prospective, parallel, double blinded, randomized clinical trial.

## **2.8.2 Study Scheme**

- Patients diagnosed with severe cerebral palsy were included in the study.
- Assignment to experimental group and control group when consent to the study
- Radiologic and clinical evaluation were performed to evaluate hip dislocation.
- The experimental group manufactured and applied hip joint wearable medical devices and continued the existing rehabilitation treatment.
- The control group continued the existing rehabilitation treatment.
- After 6 months and 1-year, clinical evaluation and radiological evaluation were performed to determine effectiveness.
- 

## **2.9 Study Population**

### **2.9.1 Inclusion Criteria**

Subjects must satisfy all of the following criteria to be included in the study

- I. age 1 to 15 years
- II. Gross Motor Function Classification System (GMFCS) IV and V
- III. quadriplegia or diplegia for more than 6 months
- IV. patients who have provided written consent with permission of the child and caregiver

### **2.9.2 Exclusion Criteria**

- I. In the event that the study was discontinued at the request of the subject or his/her representative
- II. In case of concurrent use of surgery, drug, or medical device that may affect clinical trial results
- III. If clinical trials are not properly conducted
- IV. In case the initial and late evaluation cannot be performed due to the absence of the subject
- V. Withdrawal of consent at the request of the subject or his/her representative
- VI. In case tracking is not possible due to non-scheduled visit
- VII. In case the subject dies due to reasons not related to the clinical trial
- VIII. When the investigator determines that the suspension of the test is beneficial to the subject
- IX. If the other investigator determines that there is a problem with the clinical trial

## **3.0 Data Safety Monitoring Plan**

### **3.1 Data Safety Monitoring Plan**

3.1.1 Responsibility of Data and Safety Monitoring: [name], The Principal Investigator

3.1.2 Practice of Data and Safety Monitoring: [name], The Sub- Investigator

Risk occurrence of this study is low since only one evaluation of X-ray and brace(elastic

bandage) is performed. This study is corresponded to a low risk study. Measure pain and discomfort before and after the test. To decide continue, change or discontinue of the study, use Numerical Rating Scale (NRS) as a key validation variable.

If the pain and the discomfort last 3 days after the test, perform additional test and confirm safety. The test fee should be paid by the insurance that have signed up for. To manage this, [name] professor is appointed as the monitoring manager and the principal investigator and the sub-investigator perform monitoring every six months. In the adverse event during the study, if the case is a serious adverse effect, report it to the IRB immediately and if the case is a minor adverse effect, the principal investigator and the sub-investigator perform monitoring first and report it to the IRB.

#### 3.1.3 Notifying IRB, principal investigator and Regulatory Authorities

- I. Adverse drug effect/adverse medical device effect report (fatal/life-threatening): Within 7 days (Initial report), within 8 days (tracking report)
- II. Adverse drug effect/adverse medical device effect report (not fatal/life-threatening): Within 15 days
- III. Safety information report: At least once every 6 months
- IV. Report of unexpected adverse reactions: Within 15 days

#### 3.1.4 Criteria for discontinuance of the study

- I. Discontinue the study when the target study data is obtained.
- II. If the number of study subjects could not be recruited within the IRB approval period, determine the discontinuation or alternation of the study.
- III. If the study is discontinued, the subjects follow the treatment procedures of the correspond hospital.

### 4.0 General statistical considering

- 4.1 This clinical trial uses a two-sided hypothesis for the test of difference in effectiveness. It is defined as a two-sided hypothesis, as stated in the section "Sample size calculation". ( $H_0: U_t = U_c$ ,  $H_1: U_t \neq U_c$ ).
- 4.2 The statistical method is to test normality using the Kolmogorov-Smirnov test, then test parametric or Wilcoxon rank-sum test (nonparametric test) depending on the normal distribution.

- 4.3 The number of observations, mean, standard deviation, median, minimum, and maximum values are presented for continuous variables, and frequency and percentage are presented for categorical data.
- 4.4 If a missing value occurs during validity analysis or a missing value occurs due to the elimination of the subject before the clinical trial is completed, this study measures the validity evaluation only once in the early and late period, and analyzes only the observed data (observed processes) without any correction to the missing values.
- 4.5 However, other safety assessment and other data are analyzed using data that do not replace missing values.
- 4.6 Assessment of effectiveness
- This clinical trial evaluates the p-value  $\leq 0.05$  as statistically significant results after conducting a two-sided test with either a T-test or a Wilcoxon rank-sum test.
- 4.7 Definition of the Evaluation and Analysis Group
- The main analysis group of this clinical trial is Full analysis set, the additional analysis is for per-protocol set, and the data on stability is analyzed for safety.

# Statistical Analysis Plan, Version 13.0

## 1.0 Introduction

This Statistical Analysis Plan (SAP) describes the statistical analyses planned to address the objectives of the clinical trial. It details the analyses that will be performed to accomplish these objectives. This SAP defines variables and identifies methods and algorithms used to populate the tables, figures, and listings that are included in reports for this study.

## 2.0 Study Design

### 2.1 Objectives

#### 2.1.1 Primary Objectives

The primary purpose of this study is to investigate the purpose of our study was to investigate the efficacy of newly designed hip protection brace applying biomechanical factor for preventing progressive hip displacement in patients with severe CP in a single-blinded randomized clinical trial (RCT).

#### 2.1.2 Secondary Objectives

The second purpose is to investigate the safety of hip protection brace.

### 2.2 Study Hypotheses

Our hypothesis is that hip protection brace can stabilize the hip joints, reduce the activation of hip adductors, and assist the protective function of ligaments and muscles around hip joints, thereby decreasing the progression of hip dislocation.

### 2.3 Sample Size Determination

#### 2.3.1 Statistical Hypotheses

the null hypothesis is as following.

$H_0$  = There is no meaningful relationship in migration index (MI) between the two groups. ( $H_0: U_t = U_c$ ).

$H_1$  = There is significant differences in MI between the two groups. ( $H_1: U_t \neq U_c$ ).

$U_t$  = MI (Post, test group) - MI (Pre, test group),  $U_c$  = MI (Post, control group) - MI (Pre, control group).

#### 2.3.2 Sample Size Determination

A. The calculation of the sample size is based on the previous epidemiologic study ([name] IS, Park D, Ko JY, [name] JS. Are Seating Systems With a Medial Knee Support Really Helpful for Hip Displacement in Children With Spastic Cerebral Palsy GMFCS IV and V? *Arch Phys Med Rehabil* 2019; **100**(2): 247-53.).

B. In this study, the annual progression of MI in patients with severe cerebral palsy (GMFCS IV and V) was measured to be  $7.83 \pm 8.73$  %. Assuming the MI decreased by 80 % applying Hip protection brace, the MI of the study group was set to  $1.566 \pm$

8.73 %.

C. We used PASS 15.0 for two-sample T-Test assuming equal variance.

D. With an  $\alpha$  of less than 0.05 in the two-tailed tests and a power of 80%, the target sample size of each group is 32 patients.

E. Considering a dropout rate of 5 %, the final sample size was determined to be 68 patients per group.

F. This clinical trial compares the post-treatment changes between the study and the control groups. This study was the superiority trial to show the significant improvement of the MI in the study group than the control group.

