| Study period                 | IRB approval date ~ 2 years                                                                                                                                                                                                                                                                                                                                                                                                                                                                                                                                                                                                                                                                                                                                                                              |
| Study subject                | Children aged 1 to 10 years with spastic cerebral palsy of GMFCS IV and V                                                                                                                                                                                                                                                                                                                                                                                                                                                                                                                                                                                                                                                                                                                                |
| Number of study subjects     | 68 people (34 people in the experimental group, 34 people in the control group )                                                                                                                                                                                                                                                                                                                                                                                                                                                                                                                                                                                                                                                                                                                         |

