### **4) Target number of subjects and calculation basis**

- GMFCS IV and V patients were combined before wearing auxiliary equipment, MI progression / year was measured to be  $7.83 \pm 8.73\%$  (set as a control group) (APMR 2019, IS [name], JS [name], etc.) when data.)
- In this study, the MI of the experimental group was set to  $1.566 \pm 8.73\%$ , assuming that the MI decreased by 80% when wearable auxiliary medical devices were worn.
- When the number of study subjects calculation program (PASS 15.0) was used with Level of significance = 5%, Power = 80%, and Type of test = two-sided, the total sample size was calculated as 32 patients per group and 64 patients in total, and 5% of Considering the dropout rate, a total of 68 experimental and control groups will be recruited.

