### 11) Control group setting and randomization method

Experimental group and the control group, a block randomization method is adopted.

Randomization was performed using Microsoft Excel program. A total of 68 study subjects (34 in the experimental group, 34 in the control group) were randomly assigned to a block with a block size of 4 and an allocation ratio of 1:1. In addition, in order to stratify GMFCS IV and V, 68 GMFCS IV and V are assigned respectively.

In the header of cells C4, D4, E4, and F4 of the Excel spreadsheet, enter Sequence, Random number, Block, and Group, respectively. ① Enter the numbers from 1 to 68 in cell C, which is the Sequence column, in order, and ② set the seed (GMFCS IV: 11074, GMFCS V: 11075) using the random number generation function of the data analysis tool for reproducibility in D of the Random number column. to assign a random function. ③ In Block column E, repeat the numbers from 1 to 17 in order. ④ In the Group column, input the experimental group and the control group by 34 consecutively. Then, drag from C4 to F4 to select it, and select Home -> Sort & Filter -> Filter. When a scroll bar appears in each cell, select ascending sort by clicking the scroll bar of E4, and then click the scroll bar of E4 to sort in ascending order to complete the randomization table (Kang, 2017).

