### 1.3 Randomization and Enrollment

In order to prevent an imbalance in the number of study subjects between the experimental group and the control group, a block randomization method is adopted. Randomization was performed using Microsoft Excel program. 24 GMFCS IV and 18 GMFCS V subjects were randomly assigned to two groups with a block size of 4 and an allocation ratio of 1:1. In the header of cells A1, B1, C1, and D1 of the Excel spreadsheet, enter Sequence, Random number, Block, and Group, respectively. ① Enter the numbers from 1 to 24 and 1 to 18 in cell A, which is the Sequence column, in order, and ② enter the function = Rand() in B of the Random number column to assign a random function. ③ In block column C, repeat the numbers 1 to 6 and 1 to 4 in order. At this time, the numbers 1 to 4 or 6 are repeated 4 times, which means that 24 and 18 study subjects were assigned a block size of 4. ④ In the Group column, input the experimental group and the control group, respectively, followed by 12 and 9 people. Then, drag from B1

to D1 to select it, and select Home -> Sort & Filter -> Filter. When there is a scroll bar in each cell, click the scroll bar in C1 to select ascending sort, and then click the scroll bar in C1 to sort in ascending order to complete the randomization table (Kang, 2017). A random number table is created, and a new random function is generated at the start of the study. At this time, the random number on the sheet may change and the assignment may be changed, so copy or capture the value and keep it.

Enrollment : competitive enrollment

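### SAP v13.0 states 68 patients per group where its own calculation gives 68 in total, and its randomisation section still describes the superseded 42-subject list

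*Combined protocol and SAP*

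**What the plan says.** **Sample size in SAP v13.0, section 2.3.2.** Item B takes an annual progression of the migration index (MI) of 7.83 ± 8.73% for the control group. For the brace group: "Assuming the MI decreased by 80 % applying Hip protection brace, the MI of the study group was set to" 1.566 ± 8.73%. Item C adds: "We used PASS 15.0 for two-sample T-Test assuming equal variance". Item D specifies an alpha "of less than 0.05 in the two-tailed tests and a power of 80"%, and arrives at 32 patients per group. Item E concludes: "Considering a dropout rate of 5 %, the final sample size was determined to be 68 patients per group".

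**Sample size in the current protocol (version 13.0).** Section 10, item 4, uses the same inputs and reports that "the total sample size was calculated as 32 patients per group and 64 patients in total", then allows 5% dropout and recruits 68 in total. The Study Overview gives "68 people (34 people in the experimental group, 34 people in the control group"). The inclusion criteria in section 10 and the multi-center item in section 12 also give 68 as the total.

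**Randomisation in SAP v13.0, section 1.3.** "24 GMFCS IV and 18 GMFCS V subjects were randomly assigned to two groups with a block size of 4". The list is built with Excel's Rand() function, and the groups are entered as 12 and 9 per arm in the two strata.

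**Randomisation in the current protocol, section 12, item 11.** "A total of 68 study subjects (34 in the experimental group, 34 in the control group") are allocated 1:1 in blocks of 4. Each GMFCS level has its own 68-number sequence, with 17 blocks and a fixed seed (11074 for level IV, 11075 for level V).

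**The concern.** The SAP pre-specifies the analysis, and a reader should be able to take the planned number of children and the method of allocation from it. On both points the current SAP disagrees with the current protocol. On the first it also disagrees with its own preceding line.

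Someone who checks a 68-child trial against this SAP would find that it enrolled half the stated target of 136, or 26 more children than the stated allocation list can hold (68 − 42). Someone who tried to reproduce the allocation from the SAP would have the wrong list length, no seed and the wrong stratum sizes.

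**Working it through.** **Inputs** (SAP v13.0, section 2.3.2, B to E): control mean 7.83; brace mean 7.83 × (1 − 0.80) = 1.566; common SD 8.73; two-sample t-test with equal variance; two-sided alpha 0.05; power 80%; dropout 5%.

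**1. Reproduce the plan's 32 per group.**
- Difference: 7.83 − 1.566 = 6.264. Standardised effect: 6.264 / 8.73 = 0.7175.
- Normal approximation: n = 2 × [(1.960 + 0.842) × 8.73 / 6.264]² = 30.5, so 31 per group.
- The SAP names a t-test, so the noncentral t is the right check, with df = 2n − 2 and noncentrality 0.7175 × √(n/2). At n = 31 the noncentrality is 2.825 and power is 79.4%. At n = 32 it is 2.870 and power is 80.7%.
- The smallest n that reaches 80% is 32 per group, as item D and the protocol state.

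**2. Apply the 5% dropout.**
- Per group: 32 / 0.95 = 33.7, so 34.
- In total: 64 / 0.95 = 67.4, so 68.
- In reverse: 34 × 0.95 = 32.3 evaluable per group, which covers the 32 required.
- The cruder inflation n × 1.05 gives the same result: 33.6 (34) and 67.2 (68).

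**3. Test whether 68 per group could have been meant.**
- Going from 32 to 68 per group needs dropout of 1 − 32/68 = 52.9%, against the stated 5%.
- Changing the design settings does not reach it either. By the normal approximation, a one-sided test needs 25 per group, 90% power needs 41 and 95% power needs 51.

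**4. Power of the planned trial.** With 32 evaluable per group it is 80.7%. With all 34 per group evaluable it is 83.0%.

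**5. Compare the two randomisation texts.**

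| Feature | SAP v13.0, 1.3 | Current protocol, 12, item 11 |
|---|---|---|
| Children to allocate | 24 + 18 = 42 | 68 (34 + 34) |
| List for each stratum | 24 slots (IV), 18 slots (V) | 68 slots each |
| Blocks of 4 | 6 and 4 | 17 each (17 × 4 = 68) |
| Random numbers | Rand(), no seed | seeds 11074 and 11075 |

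The SAP procedure is that of SAP v2.0, section 2.6, which served the 42-patient design. The amendment list at the end of the SAP records the change of sample size but none to the randomisation section. This fits a section that was carried over and not updated.

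**The case against.** The best defence is that this is a slip which nobody would act on. The calculation is right. A reader can see within 2.3.2 that 32 per group with 5% dropout cannot become 68 per group. The protocol, which governs enrolment, consistently says 68. All of this stands, and it limits the point to what the SAP states; the design itself is not at fault. It does not make the SAP correct, because both passages are in the body of the current version.

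A reader might be tempted to go further, in ways that the documents do not support:

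- **The trial was meant to enrol 136.** The protocol's two 68-slot lists do add up to 136 slots, but that is list length. Recruitment is competitive and the split between GMFCS levels is not fixed in advance. The same section gives 68 children, 34 per arm.
- **The trial is under- or over-powered.** Power would be 62.1% with 42 children and 98.6% with 136, but the current protocol plans neither number.
- **The SAP carries three conflicting sizes.** The 32 per group is the evaluable number before dropout and is meant to differ from the enrolled number. The stray figures are two: 42 and 68 per group.
- **The slip would decide when recruitment ends.** SAP 3.1.7 stops the study once the target data are obtained, but gives no number there.
- **The list faults belong here.** Eighteen slots do not divide into blocks of 4, but that disappears once section 1.3 is replaced. The sort instruction names the block column twice in both the SAP and the protocol, so it is not a mismatch between them and would have to be taken up separately in both.

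**Conclusion.** Wrong as written, in two places in SAP v13.0. Section 2.3.2 E doubles the final size: 136 children instead of 68. Section 1.3 describes a list that is 26 slots short of the planned enrolment and differs from the protocol in stratum sizes, list length and seeding.

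The sample-size calculation holds. The planned 68 children keep the stated 80% power under the plan's own assumptions: an 80% reduction in annual MI progression, a common SD of 8.73, a two-sided 5% t-test and 5% dropout. Whether those assumptions are realistic is a different question and is not judged here. The documents do not show that enrolment or allocation actually followed the SAP text rather than the protocol.

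**What to change.** 1. In SAP 2.3.2 E, give the final sample size as 68 patients in total (34 per group). Make the same correction in the Version 13.0 column of the SAP's amendment list, which repeats the error.
2. Replace SAP 1.3 with the randomisation procedure of the current protocol, section 12, item 11: separate lists for GMFCS IV and V, 68 slots each, 17 blocks of 4, 1:1 allocation, seeds 11074 and 11075, and enrolment of 68 overall. Keep the existing line on competitive enrolment.
3. Record the change to section 1.3 in the SAP's amendment list.

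The cost is SAP wording only. It needs no new calculation, no additional children and no change to the design.
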